### Primary outcome

The primary outcome was the incidence of PONV 3 days after surgery. PONV is defined as a spectrum incorporating some combination of nausea, vomiting and/or retching in the postoperative period. Nausea and vomiting scales are also used to grade PONV severity [19]. The dosage and frequency of use of postoperative antiemetic drugs (metoclopramide or 5-hydroxytryptamine antagonist) were also recorded for analysis.

### Secondary outcomes

Variables indicating recovery status included the time to spontaneous respiration, awakening, eye opening and extubation after stopping anaesthetic agents. The scales used for patient pain, sedation level and overall recovery assessment included the visual analogue score (VAS), Modified Observer’s Assessment of Alertness/Sedation (MOAA/S), Bruggrmann Comfort Scale (BCS) [20] and 15-item Quality of Recovery Questionnaire (QoR-15) [21]. Delirium and cognition were assessed with the Confusion Assessment Method and Mini-Mental State Examination [22, 23]. Anxiety and depression were evaluated with the Hospital Anxiety and Depression Scale [24]. All scales were assessed at 0, 2, 4, 8, 24 and 72 h after waking. The total amount of propofol consumption, all drugs used during anaesthesia and analgesics for postoperative pain management were recorded. Side effects or adverse events were recorded for 3 postoperative days, and thereafter, the hospital stay time was recorded. The intraoperative variables collected included anaesthesia and surgery time, intraoperative medication, blood loss, fluid and blood transfusion, urine output, mean arterial pressure (MAP) and heart rate, time and duration of low blood pressure (MAP < 60 mmHg) and nociceptive level of SPI. The average percent change to baseline in mean arterial pressure and heart rate was also calculated. Percent change for arterial pressure = (MBPT1−*x* − MBPT0)/MBPT0 × 100; percent change for HR = (HRT1−*x* − HRT0)/HRT0 × 100. The recorded time points are as follows: after entering the operation room, patients were allowed to be quiet for 10 min, and blood pressure and heart rate were measured twice (15 min apart) and the average values were recorded as the basic blood pressure and heart rate (T0), when TCI propofol reached equilibrium (T1), 3 min after sufentanil or esketamine infusion (T2), immediately after intubation (T3), 5 min after intubation (T4), time to pneumoperitoneum (T5) and then every 15 min (T6−*x*) until the end of the surgery.

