### Ethics issues

This study was approved by the Ethics Committee of Shidong Hospital, University of Shanghai for Science and Technology (Ethics number: YPSDKY2021-02-009). Designated doctors explained this trial to interested potential participants in detail and provided them with the informed consent form. Participants were given at least 6 h to decide whether they wished to participate in the trial. The informed consent form was signed by the participant or his or her trustee or guardian, and consent could be withdrawn at any time during the trial. Written informed consent and the patient’s baseline data were obtained before randomization. Moreover, participants were encouraged to contact the research team if they had any health concerns during the trial.

The schedule of enrolment, intervention and assessment is reported according to the SPIRIT statement (Fig. 1).

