**Fig. 1 Fig1:**
[figure not shown]
Schedule of enrolment, intervention and assessment according to the Standard Protocol Items: Recommendations for Interventional Trials (SPIRIT) statement. Time points for implement of the study: *t*_−1_: when enrolled, *t*_0_: allocation, *t*_1_: before anaesthesia, *t*_2_: TCI propofol reached equilibrium, *t*_3_: in 3 min after sufentanil or esketamine infusion, *t*_4_: immediately after intubation, *t*_5_: in 5 min after intubation, *t*_6_: pneumoperitoneum, *t*_7−*x*_ in each 15 min till the end of the surgery; *t*_*a*−*g*_ refers to 0, 2, 4, 8, 24, 48 and 72 h after anaesthesia

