According to a recent study on Chinese patients, the administration of esketamine as a relatively small dose was generally safe for anaesthesia without consideration of sex differences [32]. In fact, several advantages of esketamine in clinical anaesthesia have recently been proven. First, it creates less impairment on patients’ spontaneous breathing and airway reflexes as well as circulation stability due to an increase in sympathetic tone. In addition, Eberl et al. [17] reported that low-dose esketamine reduces the total amount of propofol necessary for sedation during ERCP while proving satisfactory sedative effects. Furthermore, many studies report that a combination of propofol with ketamine may result in a better quality of sedation and analgesia, with shorter recovery time, better satisfaction of patients and fewer respiratory or cardiovascular side effects [33]. Despite all these benefits, one widespread concern of esketamine is that it can produce psychotomimetic effects that may be associated with cognitive impairment [13].

In this trial, we hypothesized that OFA with esketamine could reduce the PONV rate after laparoscopic surgery based on several possible underlying mechanisms. On the one hand, it certainly reduced the consumption of opioids perioperatively, which has been proven to be one of the main risk factors for PONV [34]. On the other hand, esketamine is also known for its effective effects in maintaining spontaneous breathing and airway reflexes during anaesthesia; in addition, it can increase sympathetic tone and result in less hypotension and cardiac depression [35]. The reduced interference of esketamine on respiratory and circulatory systems during surgery also provides better conditions for ERAS in patients.

However, research on the advantages or disadvantages of esketamine in surgical anaesthesia remains deficient, and further randomized trials with larger sample sizes are urgently needed in this area. In this study, we also plan to investigate intraoperative circulatory stability as well as other recovery indices for esketamine in anaesthesia for laparoscopic appendectomy and cholecystectomy.

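### No preoperative MMSE, CAM, HADS or QoR-15 is stated, so the scheduled scores cannot show new decline within a patient and give up baseline precision; the two stated schedules also differ

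*Protocol article*

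**What the plan says.** All places are in the protocol article.

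- **Instruments (Secondary outcomes).** VAS, MOAA/S, BCS and QoR-15 cover pain, sedation, comfort and recovery. For the rest: "Delirium and cognition were assessed with the Confusion Assessment Method and Mini-Mental State Examination", and "Anxiety and depression were evaluated with the Hospital Anxiety and Depression Scale".
- **Times (Secondary outcomes).** "All scales were assessed at 0, 2, 4, 8, 24 and 72 h after waking".
- **Times (Fig. 1 legend).** The postoperative series "refers to 0, 2, 4, 8, 24, 48 and 72 h after anaesthesia". The legend also has points at enrolment, at allocation and before anaesthesia. The grid showing what is done at each point is not available.
- **Baseline.** Ethics issues says: "Written informed consent and the patient’s baseline data were obtained before randomization". It does not list those data. Secondary outcomes defines a baseline (T0) and a percent-change formula for arterial pressure and heart rate only.
- **Screening (Inclusion and exclusion criteria).** A preoperative neuropsychiatric inventory is used to exclude patients with mental disorders. It is not one of the outcome scales.
- **Analysis (Statistical analysis).** Continuous outcomes are compared by t test or Mann-Whitney test. No change score or baseline-adjusted comparison is stated for the scales.
- **Relevance (Discussion).** One widespread concern about esketamine is that "it can produce psychotomimetic effects that may be associated with cognitive impairment".

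**The concern.** Cognition, delirium and mood are the secondary outcomes closest to the safety concern that the Discussion raises about esketamine. Saying that a patient's cognition or mood became worse requires that patient's earlier level. Every stated time for MMSE, CAM, HADS and QoR-15 is after waking, so a low MMSE or a high HADS at 24 or 72 h cannot be separated from the patient's usual level.

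The schedule also gives these four instruments at the moment of waking, alongside a sedation scale. A poor MMSE or a positive CAM at 0 h may partly reflect emergence. Time to awakening is itself an outcome, so emergence may differ between arms, and an early difference in cognition scores would then be hard to interpret.

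Finally, a comparison of postoperative scores alone leaves out a covariate that is cheap to collect and could narrow the confidence intervals.

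**Working it through.** **1. Count of the stated times.**

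| Source | Times (h) | Origin | Number | At or before 8 h | Before surgery |
|---|---|---|---|---|---|
| Secondary outcomes | 0, 2, 4, 8, 24, 72 | waking | 6 | 4 | none stated |
| Fig. 1 legend, postoperative series | 0, 2, 4, 8, 24, 48, 72 | anaesthesia | 7 | 4 | grid not shown |

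The lists differ by the 48 h point and by the time origin. The origin matters most at 0 h: the interval between the end of anaesthesia and waking is measured in the trial and may differ by arm.

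**2. Is a preoperative score stated anywhere?**

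- Ethics issues: baseline data before randomisation, contents not listed.
- Inclusion and exclusion criteria: a different instrument, used only to exclude.
- Secondary outcomes: T0 for arterial pressure and heart rate, none for any scale.
- Fig. 1 legend: pre-anaesthesia time points exist, contents unknown.

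The supportable statement is that none is stated, not that none was done.

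**3. What a baseline would be worth for the continuous scores.** The documents give no correlation r between preoperative and later scores, so r is an assumption, shown from 0.3 to 0.7. Take the variance of the postoperative score as 1.

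- Adjusted for baseline (ANCOVA): residual variance = 1 − r²
- Simple change score: variance = 2(1 − r)
- Equivalent sample-size factor for ANCOVA = 1/(1 − r²)

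| r | ANCOVA variance | Reduction | Sample-size factor | Change-score variance |
|---|---|---|---|---|
| 0.3 | 1 − 0.09 = 0.91 | 9% | 1.10 | 1.4 |
| 0.5 | 1 − 0.25 = 0.75 | 25% | 1.33 | 1.0 |
| 0.7 | 1 − 0.49 = 0.51 | 49% | 1.96 | 0.6 |

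Two things follow. Adjustment never does worse than the unadjusted score in this table, whereas a simple change score does worse at r = 0.3 and only breaks even at r = 0.5. So a preoperative score should enter as a covariate. The formulas concern continuous scores under linear adjustment; they say nothing about a yes/no CAM result.

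**4. Does the primary outcome depend on this?** No. The sample size of 139 per group rests on PONV rates of 37.3% and 20%, two-sided α = 0.05 and 90% power. With unpooled variances, (0.373 × 0.627 + 0.20 × 0.80) × (1.960 + 1.282)² / 0.173² rounds up to 139, the stated figure. No scale enters it.

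**The case against.** The strongest case against has five parts.

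- **A preoperative administration may exist.** The baseline data are not listed and the Fig. 1 grid is not shown. An article may also leave such detail to the full protocol. This stands. A reader might infer that no scale was given before surgery; the documents do not establish that. What remains is that the text fixes the times for all scales and includes no preoperative one.
- **The plan never promises change scores, and randomisation protects the comparison.** This stands as well. A reader might infer that the between-arm results are biased; they are not. The loss is in precision and in recognising decline within a patient. Screening out mental disorders in patients aged 18–50 makes prior impairment less likely but does not measure each patient's level.
- **The effect of sedation on early scores is an inference.** A reader might conclude that the first scores simply measure residual sedation. The documents do not say so, and MOAA/S at the same times allows sedation to be read beside each score. The defensible claim is that early MMSE, CAM, HADS and QoR-15 scores, especially at 0 h, may partly reflect emergence. Early VAS, BCS and MOAA/S are not in question.
- **The precision gain is assumed.** It is. At r = 0.3 it is only 9%, and if MMSE sits near its ceiling in this young, screened population its correlation may be low.
- **It may be late.** Trial status gives first inclusion in October 2021 and expected completion in September 2022, and the Abstract describes enrolment in the past tense. This limits how many patients could still provide a baseline, and so limits the benefit in this trial.

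Nor does the Discussion make cognitive impairment the main concern with esketamine: it names psychotomimetic effects as one widespread concern and links them to cognition only as a possibility.

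**Conclusion.** The point holds in a limited form. As written, the schedule states no preoperative MMSE, CAM, HADS or QoR-15, so new cognitive or mood decline cannot be identified within a patient. The randomised comparisons remain valid but forgo baseline precision: a 9% to 49% reduction in the residual variance of continuous scores if r lies between 0.3 and 0.7, which the documents neither support nor contradict. The 0 h cognition, delirium, mood and recovery scores need cautious interpretation.

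Separately, and without any assumption, Secondary outcomes and the Fig. 1 legend give different postoperative times (six against seven, with 48 h only in the legend) and different time origins, and must be reconciled.

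Only secondary outcomes are affected. The change is worth making, but the primary outcome and its sample size do not depend on it.

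**What to change.** 1. Administer MMSE, CAM, HADS and QoR-15 once before randomisation. If Fig. 1 already includes this, correct Secondary outcomes to say so.
2. Compare arms on the continuous scores at 24 and 72 h with the preoperative score as a covariate, not as a simple change score. Use a missing-baseline indicator for patients already enrolled without one. If no patient has a baseline, compare postoperative scores as planned and state that decline within a patient cannot be assessed.
3. Keep the early assessments. Report early MMSE and CAM results beside the concurrent MOAA/S, and interpret the 0 h values as emergence. Do not exclude patients according to MOAA/S: it is measured after randomisation and treatment may affect it, so the remaining patients would be a selected group in each arm.
4. Reconcile Secondary outcomes with the Fig. 1 legend: state whether 48 h is an assessment time for the scales, and whether time runs from waking or from anaesthesia.

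The cost is one short questionnaire session for each patient still to be enrolled. Items 3 and 4 need no new data collection unless 48 h is confirmed as an assessment time that is not yet in use.

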### Safety management and adverse events

An adverse event refers to an untoward medical occurrence that happens during the trial. Adverse events include but are not limited to PONV, mental disorders, respiratory depression or cardiocirculatory instability. All adverse events were treated immediately. All adverse events were documented and discussed in data monitoring committee (DMC) meetings.

### Data collection and management

The collected data including sociodemographic characteristics, peri-operative variables and various questionnaires are as mentioned above. To improve data quality, we set up a data monitoring committee consisting of a medical doctor, a statistician and a nurse. All survey data were checked for logical or clerical errors, with significant errors will be verified by the participant. Final survey data completed by all participants will be saved in a secure computer only used for saving data.

### Data monitoring

The data monitoring committee (DMC), composed of statisticians, principal investigators from each centre and representatives from the ethics committee, will be responsible for data monitoring. Members of the data monitoring committee are independent of the sponsors. The written report on trial progress from each centre will be submitted to the committee quarterly. Cases of adverse events and unexpected scenarios will be discussed at committee meetings.

### Sample size calculation

The sample size was calculated with PASS 15.0 (Number Cruncher Statistical Software, LLC, Kaysville, UT, USA). The hypothesis of this trial is that esketamine could be associated with fewer side effects of PONV than opioid anaesthesia. With *α* = 0.05 and a power of 90%, we assumed that esketamine anaesthesia may reduce the PONV rate from 37.3 to 20% according to a study by Ziemann-Gimmel et al. [25]; thus, a sample size of 139 for each group would be needed. According to previous studies, the general incidence of vomiting after surgical anaesthesia is approximately 30%, while the incidence of nausea is approximately 50% [26–28]. Therefore, proportions of 37.3% and 20% of PONV of patients in the F group and E group, respectively, were used to calculate the sample size.

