**Methods/design:**

The study was designed as a prospective, randomized, controlled, multicentre trial. A total of 278 patients were enrolled; participants were nonsmoking female patients aged 18–50 years and scheduled for laparoscopic appendectomy or cholecystectomy, ASA at I–III, with no serious physical or mental diseases. Both groups received usual perioperative care except for the analgesic medication of either esketamine or sufentanil. The primary outcome was the incidence of PONV 3 days after surgery. Secondary outcomes included recovery status, pain, sedation level and overall recovery, delirium and cognition, anxiety and depression and total consumption of analgesic agents.

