### Inclusion and exclusion criteria

The inclusion criteria were as follows: (1) nonsmoking female patients who were 18–50 years old with a planned laparoscopic appendectomy or cholecystectomy from October 1, 2021, to October 1, 2022; (2) American Society of Anaesthesiologists (ASA) classification I–III; (3) no analgesic/sedative medication was used within 24 h before surgery; (4) no serious endocrine, cardiovascular and respiratory diseases before surgery; (5) no mental abnormality; and (6) provision of signed informed consent.

The exclusion criteria included patients who (1) had an allergic history of anaesthetic drugs or contraindications of esketamine, nonsteroidal anti-inflammatory drugs or dexmedetomidine; (2) had mental disorders, preoperatively screened using a neuropsychiatric inventory; (3) had poorly controlled or untreated hypertension with resting arterial pressure over 180/100 mmHg; (3) had addiction or dependence on opioid or hypnotic drugs; and (4) had respiratory infection or asthma before surgery.

Patients who were enrolled but met one of the following criteria were excluded from the study: (1) incomplete case report form or lost to follow-up and failed to make an effective and safety assessment, (2) change of anaesthesia method due to unexpected incident or surgery requirement during the surgery, (3) operation could not be continued due to unexpected incident during the surgery and (4) other diseases post-surgery required urgent treatment.

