### Sequence generation and allocation concealment

Blocked randomization was conducted. A randomization sequence was generated using a computerized random number generator, and patients who met the enrolment criteria were randomized in a 1:1 ratio to either the control or esketamine anaesthesia group. Once the patient was qualified for the study, the project coordinator opened a sealed opaque envelope with random serial numbers. Only the statistician and the project coordinator knew the treatment allocation of each participant.

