### Statistical analysis

Statistical analyses will be performed using SPSS 25.0 (IBM SPSS Statistics, Armonk, NY). An intention-to-treat (ITT) approach will be used to analyse the data. All data will be checked for normal distribution using the Kolmogorov test. For normally distributed data, continuous variables will be analysed using the independent Student’s *t* test, and the variables will be presented as the mean ± standard deviation (SD). Nonnormally distributed data will be compared using the Mann‒Whitney *U* test where appropriate, and data will be presented as the median and interquartile range (IQR). For categorical variables, cross-tabulation and the Pearson chi-squared test will be applied, and variables will be categorized as numbers and/or percentages of the total. A logistic regression model will be applied to detect any potential confounding factors. To compare the continuous measurements of HR and NIBP between the groups, the area under the curve (AUC) for each value will be calculated over the different measurement time points during the procedure. To compare the continuous measurements of HR and NIBP between the groups, the area under the curve (AUC) for each value will be calculated over the different measurement time points during the procedure. Missing data are neglected or multiple imputation will be used when > 40% and identified as missing, not at random. A *p* value < 0.05 with two tails will be considered statistically significant.

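### The 139 per group gives 90% power only if every randomised patient is analysed; enrolment has no margin, and applying the plan's own exclusions would lower power modestly.

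*Protocol article*

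**What the plan says.** All places are in the protocol article.

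- **Sample size calculation.** The inputs are alpha = "0.05 and a power of 90"%, and "proportions of 37.3% and 20% of PONV of patients in the F group and E group, respectively, were used to calculate the sample size". The result is that "a sample size of 139 for each group would be needed". No loss rate and no inflation are mentioned.
- **Abstract, Methods/design.** "A total of 278 patients were enrolled", which is 2 x 139.
- **Sequence generation and allocation concealment.** Patients were "randomized in a 1:1 ratio to either the control or esketamine anaesthesia group".
- **Inclusion and exclusion criteria, last paragraph.** Patients already enrolled are excluded on four grounds. The first is "incomplete case report form or lost to follow-up and failed to make an effective and safety assessment". The others are a change of anaesthetic method, an operation that could not continue, and another postoperative disease needing urgent treatment.
- **Dropout criteria.** Withdrawal of consent and loss to follow-up are foreseen.
- **Statistical analysis.** The section adopts intention to treat, uses the Pearson chi-squared test for categorical variables, and takes p "< 0.05 with two tails will be considered statistically significant". On incomplete data it says: "Missing data are neglected or multiple imputation will be used when" more than 40% is missing and the data are judged missing not at random.

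**The concern.** The number needed for analysis and the number enrolled are the same, so the stated power has no slack. The plan nevertheless describes several ways in which a randomised patient can leave the analysis. Three of the four exclusion grounds can arise only during or after surgery, and therefore after randomisation. The article describes no replacement of excluded patients.

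The stated power matters most if the PONV comparison is not significant. Readers will then use the 90% to judge how firmly a reduction from 37.3% to 20% has been ruled out. If that figure describes 278 analysed patients and fewer are analysed, the null result will be read as stronger evidence than it is.

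**Working it through.** **Inputs.** p1 = 0.373 (group F), p2 = 0.200 (group E), difference 0.173, power 0.90, 1:1 allocation. Two-sided alpha of 0.05 is taken from the Statistical analysis section, because the sample size section does not state sidedness.

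**Step 1: reproduce 139.** With unpooled variance,

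n = (z_0.975 + z_0.90)^2 x [p1(1 - p1) + p2(1 - p2)] / (p1 - p2)^2

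- (1.960 + 1.2816)^2 = 10.507
- 0.373 x 0.627 + 0.2 x 0.8 = 0.2339 + 0.1600 = 0.3939
- 0.173^2 = 0.02993
- n = 10.507 x 0.3939 / 0.02993 = 138.3, rounded up to **139**

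The stated figure is reproduced exactly, with no inflation hidden in it. The pooled-variance form gives 141.4, so 142. The gap of 3 per group is a choice of formula, not an error.

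**Step 2: margin.** 278 enrolled - 2 x 139 needed = 0.

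**Step 3: power with everyone analysed.** At 139 per group, the unpooled approximation gives 90.2% and the pooled one 89.5%. Summing the binomial probabilities of all 2 x 2 tables in which the uncorrected Pearson test rejects at two-sided 0.05 gives 89.8%. All three are 90% for practical purposes.

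**Step 4: power if patients are removed.** The article gives no loss rate, so a range is assumed. Loss is taken as equal in the two arms and unrelated to outcome, and the analysed number is 139 x (1 - loss), rounded down.

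| Assumed loss | Analysed per group | Exact Pearson power | Shortfall from 90% |
|---|---|---|---|
| 0% | 139 | 89.8% | 0.2 points |
| 2% | 136 | 89.2% | 0.8 points |
| 5% | 132 | 88.2% | 1.8 points |
| 10% | 125 | 86.3% | 3.7 points |
| 15% | 118 | 84.5% | 5.5 points |
| 20% | 111 | 82.0% | 8.0 points |

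At 10% loss the type II error is 100 - 86.3 = 13.7%, against the 10% implied by the plan.

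**Step 5: which number does the plan analyse?** Under intention to treat, a patient whose anaesthetic was changed, whose operation stopped or who needed urgent treatment afterwards stays in the analysis. Only patients without PONV data are lost. Under the last paragraph of the eligibility section, all of these patients are out. The article states both rules and does not say which one governs the primary outcome, so it does not fix where in the table the trial would sit.

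**The case against.** The strongest reply is that the plan already claims intention to treat. If that governs and PONV data are complete, all 278 are analysed and the stated power holds. This is right as far as it goes, and it is why the shortfall is conditional. It does not remove the point, because the same article excludes those patients from the study and sets missing data aside.

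A second reply is that the loss is probably small. PONV is a yes/no outcome over 3 days, with assessments ending at 72 h, and at 5% loss the shortfall is under 2 points. Nothing in the article supports the 15% and 20% rows in particular, and power stays above 80% even there. The routes also overlap: loss to follow-up appears under both exclusion and dropout, and incomplete forms and missing data will largely concern the same patients, so they should not be added together. The assumed control rate matters more: with 35% in place of 37.3%, and 20% held fixed, exact power at 139 per group is about 81%. All of this stands, and it limits the size of the point.

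A third reply is that a condensed article may leave replacement of patients to the full protocol. That is fair, and its absence is not counted against the plan. The point rests on figures and rules that the article does print.

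A reader might infer two stronger things:

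- *That 139 is miscalculated, or that the Pearson test makes the trial underpowered from the start.* Step 1 reproduces 139, and 89.8% is 90% to the precision at which power is quoted.
- *That the trial certainly fails to deliver 90%.* That would require the exclusions to be applied, or PONV data to be missing. The intention-to-treat statement leaves the first open, and the article gives no rate for the second.

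**Conclusion.** The sample size of 139 per group is correct as a no-loss figure, and enrolment equals it exactly. The stated 90% therefore holds only if all 278 are analysed. If the post-enrolment exclusions are applied, exact Pearson power falls modestly: about 88% at 5% loss, 86% at 10% and 82% at 20%.

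The direction does not depend on the loss rate, but the size does, and the article gives no rate. The figures also assume the article's own event rates, equal loss in the two arms, and loss unrelated to PONV. If exclusions were related to treatment or outcome, there would be a risk of bias as well. That is a separate matter, which power figures do not measure.

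The point is worth correcting, but it does not threaten the design.

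**What to change.** 1. **Reconcile the eligibility section with the intention-to-treat statement.** State that all randomised patients stay in the primary PONV analysis, including those meeting the four post-enrolment criteria. An analysis that applies the exclusions can be reported as a supplementary one.
2. **Restate the sample size paragraph.** Say that 278 is the number randomised, that 90% is the power if all are analysed (89.8% exactly, with the planned Pearson test), and give the expected evaluable number with its power. For example, 125 per group gives about 86%. The expected loss must come from the investigators, since the article supplies none.

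The cost is a few sentences and a slightly less favourable stated power, with no added patients. Step 1 also keeps the realised power as close to 90% as the completeness of the PONV data allows.
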